## **9.3 Procedures at Each Study Stage**

### **9.3.1 R: Recruitment of HPs**

- Invitation of hospitals to participate in study
- Provision of written information about study for senior HPs and collection of their informed consent
- Collection of senior HP data and descriptors of their hospitals and clinical units (i.e. hospital and clinic type and size)
- Randomization of senior HPs

### **9.3.2 T: Teaching of HPs**

- Teaching sessions for senior HPs according to trial arm

### **9.3.3 A: Patient Admission**

- Screening of participants according to in- and exclusion criteria
- Provision of written information about study and collection of the patients' informed consent
- Collection of patient characteristics (age, sex)

### **9.3.4 D = T0: Patient Discharge (Baseline)**

- Discharge procedure: In accordance with the checklist (see forms 5b and 5c, appendix 18.1) in intervention arm; “usual discharge care” in control arm
- Communication of
  - changes in medication (including offer of discussion) and (provisional) discharge report (including medication plan) in the intervention arm or
  - (provisional) discharge report (including medication plan) in the control arm to the patients’ GPs
- Submission of
  - discharge checklist and changes in medication, informed consent form, QoL-questionnaire and medication plan in the intervention arm or
  - informed consent form, QoL-questionnaire and (provisional) discharge report (including medication plan) in the control arm to the study center

### **9.3.5 T1: 1 Month After Discharge**

- Reporting of readmission, ED visits and GP encounters
- Submission of current medication plan and QoL-questionnaire to study center

### **9.3.6 T3: 3 Months After Discharge**

- Reporting of readmission, ED visits and GP encounters
- Submission of current medication plan and QoL-questionnaire to study center

### **9.3.7 T6: 6 Months After Discharge**

- Reporting of readmission, ED visits and GP encounters
- Submission of current medication plan and QoL-questionnaire to study center

## 10 SAFETY

### 10.1 Definition of Serious Adverse Events

Within this study, a serious adverse event (SAE) is defined as any untoward medical occurrence in a patient happening after the intervention which:

- requires inpatient treatment or extends a current hospital stay
- results in permanent or significant incapacity or disability
- is life-threatening or results in death

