## 8 STUDY INTERVENTION

### 8.1 General Information and Administration of Interventions

#### 8.1.1 Study Intervention

The intervention takes place on different levels with different target populations:

- a. *Teaching session (“Teach-the-Teachers”) for the senior HPs in charge of postgraduate training and supervision of the interns (assistant physicians)*

The purpose of this training of two hours duration is to integrate the discharge procedure (see below) into the daily work of the HPs during the study period. Consecutively, the senior HPs will teach the interns how to apply the structured discharge procedure. This will guarantee the consistency of the intervention even if the fluctuation among interns is high due to organized job rotations within hospitals.

The teaching session will address the following items:

- How to identify patients eligible (possibly in collaboration with nurses)
- How to handle the in- and exclusion criteria
- How to apply the medication review tool (discharge checklist in forms 5b and 5c, see list of study instruments in appendix 18.1) which has been previously tested (15, 32) to the medication plan of the patient before discharge by the HP
- How to involve the senior HP responsible for the interns’ supervision in the medication review, depending on the clinic’s/wards’ usual discharge procedures
- How to involve patients in the changes suggested by the HP
- How to create a discharge medication plan for the patient, after the decision is taken
- How to involve the GPs in the post-discharge phase. An offer for the GP to call the HP in order to discuss the medication plan is prepared on the discharge medication plan. This should guarantee a consensus between HP and GP in order to increase the GPs’ adoption of the changes suggested on the long term
- How to deal with the different data collection forms

- b. *The intervention at discharge*

The intern HP performs a critical review of the medication plan, supervised by his senior HP, discusses the results of this review and his suggestions with the patient and creates a discharge medication plan to be used by the patient. The patient is encouraged to consult his GP within seven days.

Furthermore, the intern HP communicates all medication changes (cessation of specific medication, change of dosage, introduction of new drugs) to the patient’s GP in written form, accompanied with an invitation to the GP to discuss any medication changes (forms 5b and 5c, see appendix 18.1).

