### **9.2.4 Assessment of Safety Outcomes**

#### **9.2.4.1 Serious Adverse Events**

For the definition of serious adverse events (SAEs) see section 10.1. Inpatient treatment and death are assessed within this study as primary or secondary outcomes, respectively, and will be recorded retrospectively.

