### 10.2 Recording and Assessment of Serious Adverse Events

Safety outcomes (readmission, ED visits, GP encounters, death) form an integral part of the study design and will be collected retrospectively at all follow up stages (1, 3 and 6 months after the intervention).

A possible causal dependence of individual SAEs on the study intervention will be assessed by the study team according the following definitions:

|                   |                                                                                                                                                                                                                                                 |
|-------------------|-------------------------------------------------------------------------------------------------------------------------------------------------------------------------------------------------------------------------------------------------|
| Unrelated: | 

• The event started in no temporal relationship to the medical intervention applied and

• The event can be definitely explained by underlying diseases or other situations.

             |
| Related:   | 

• The event started in a plausible temporal relationship to the medical intervention applied and

• The event cannot be definitely explained by underlying diseases or other situations.

 |

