### 10.3 Reporting of Serious Adverse Events

All SAEs will be summed up in the annual safety report (ASR) and submitted to the CEC. The ASR will contain a summary of the events including severity and causal relationship to the intervention and implications on the safety of participants. The enclosed letter to be provided with the ASR will contain a short summary of the status of the clinical trial.

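### The SAE definition is wider than the planned safety collection, so the completeness of the all-SAE report promised to the ethics committee is not assured

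*Protocol*

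**What the plan says.** Protocol 10.1 defines an SAE as "any untoward medical occurrence in a patient happening after the intervention which" meets at least one criterion. The criteria are that it "requires inpatient treatment or extends a current hospital stay", that it "results in permanent or significant incapacity or disability", or that it is life-threatening or fatal.

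In 8.1.1 the review tool is applied "to the medication plan of the patient before discharge by the HP".

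On collection, 9.2.4.1 states: "Inpatient treatment and death are assessed within this study as primary or secondary outcomes, respectively". Section 10.2 adds: "Safety outcomes (readmission, ED visits, GP encounters, death) form an integral part of the study design", gathered retrospectively at 1, 3 and 6 months. The visit lists agree with this. The 1-month list in 9.3.5, for example, has "Reporting of readmission, ED visits and GP encounters" together with the medication plan and the quality-of-life form. Section 5.2 and the entry for form 5d in 18.1 show that reasons for these contacts are also recorded, and 5.2 includes reasons for death.

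On reporting, 10.3 states: "All SAEs will be summed up in the annual safety report (ASR) and submitted to the CEC", with severity and causal relationship.

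**The concern.** The definition, the collection and the report are set in different sections and do not have the same scope. The definition starts at the intervention and lists several kinds of harm. Collection starts after discharge and is organized around contacts with care. The report is described as if the two coincided.

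Two things are at stake. The first is the accuracy of what the ethics committee is told: a summary presented as complete may not be. The second is where the gap falls. Section 10.2 calls an event related only if its timing relative to the intervention is plausible and it is not definitely explained otherwise. Events soon after a drug change satisfy the timing part most readily, and the days between review and discharge are the part of the window with the least recording.

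**Working it through.** No figure is stated and no arithmetic applies. The check sets each outcome named in 10.1 against every place where it could be recorded: 4.4, 5.2, 9.2.2, 9.2.4.1, 9.3.4 to 9.3.7, 10.2, 13.1.2, 18.1 and the schedule in 9.1.

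1. **New inpatient treatment after discharge.** Collected directly as readmission with its date, and with reasons (5.2, 18.1).
2. **Death.** Collected directly. Section 9.2.2 says that chasing missing data from patients, relatives, GPs and hospitals also captures deaths. Since forms are due at discharge too, a death before discharge would probably come to light the same way.
3. **Extension of a current stay.** For a readmission this adds nothing, because the readmission already qualifies. For the index stay there is no listed route. The discharge submission in 9.3.4 consists of:
   - intervention arm: checklist and medication changes, consent form, quality-of-life questionnaire, medication plan;
   - control arm: consent form, quality-of-life questionnaire, and the (provisional) discharge report including the medication plan.

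   Neither list has an event item, and the schedule in 9.1 has no safety row at discharge. The discharge report is the one document likely to show a complicated end of stay. It goes to the GP in both arms but to the study center only in the control arm.
4. **Lasting or significant incapacity or disability.** No dedicated item is listed. It is found only if it led to a readmission, ED visit, GP encounter or death and the recorded reason shows it.
5. **Life-threatening event.** The same indirect route as item 4. Seriousness is not among the listed items, although 10.3 requires a severity summary.

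Two further limits bear on the promise in 10.3. Section 9.2.5 ends safety recording when a participant withdraws or stops early. The minimum source-document list in 13.1.2 names related SAEs only, whereas 10.3 covers all of them.

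Result: of five outcomes, two are collected directly, two indirectly, and one has no listed route during the index stay.

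**The case against.** The strongest objection concerns when the window opens. The protocol speaks of an intervention at discharge and places the discharge procedure at stage T0. Section 10.2 counts the visits from the intervention, while 9.3.5 to 9.3.7 count the same visits from discharge, which treats the two as one time point. On that reading the SAE window opens at discharge and nothing from the index stay is lost. This has force: the interval may be short, and its length is not given. It does not settle the matter. Section 8.1.1 puts the review before discharge, and if the window opened only at discharge, the clause on extending a current stay would have almost nothing left to apply to.

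Second, a reader might infer that follow-up asks about contacts and death and nothing more. The documents do not support that. Reasons are recorded, and 5.2 allows them to come from GP, hospital and ED records as well as from the patient. Section 4.4 aims at complications leading to GP encounters, ED visits and deaths. Many disabling or life-threatening events after discharge would therefore surface. A serious event with no contact and no death is a small remainder.

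Third, the forms themselves are not shown, and 8.1.1 calls the discharge forms samples to be adapted with each clinic. An event item could exist. It is not listed in 9.3.4, 10.2 or 18.1, however, and if arranged clinic by clinic it would not be uniform across arms.

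Fourth, this is a category A trial with minor expected risk. That bears on how much safety collection is needed. It does not remove the need for the definition and the reporting promise to match what is collected.

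**Conclusion.** The mismatch is real but limited. The planned collection does not cover every criterion in 10.1, so completeness of the report in 10.3 is not assured. The clearest gap, an index stay prolonged after the review, rests on reading the start of the window as the review, which 8.1.1 supports and 10.2 leaves open. The indirect capture of disabling and life-threatening events does not depend on that reading.

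Three stronger conclusions might be inferred and should not be drawn:

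- The report cannot be produced. Most serious events after discharge can be reported, because readmissions and deaths are collected and reasons are recorded.
- Harm in the intervention arm will be understated. The differing discharge documents make this a risk, but nothing in the protocol shows it.
- A certain number of events will be missed. The protocol gives neither an event rate nor the length of the interval between review and discharge. The planned 1,050 patients per arm pass through that interval, but any count would rest on an outside guess.

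The primary outcome, its analysis and the sample size are unaffected. The point deserves a correction because it concerns a statement made to the ethics committee and the correction is cheap.

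**What to change.** Reconcile 10.1, 10.2, 9.2.4.1, 9.3.4 and 10.3. First state whether the SAE window opens at the medication review or at discharge. Then take one of two routes.

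(a) Match collection to the definition. Add one item to the discharge submission in both arms asking whether an untoward event after the review prolonged the stay, with its date. For control patients, who have no study review, tie the item to a comparable moment such as the setting of the discharge medication plan. Add one yes/no item to the follow-up form (5d in 18.1) for new lasting disability or a life-threatening event since the last form. Name both items in 9.2.4.1 and 10.2.

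(b) Match the promise to the collection. Limit 10.3 to what is gathered: readmissions, deaths, and complications leading to an ED or GP contact after discharge.

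Under either route, 10.3 should acknowledge that recording stops when a participant leaves the study (9.2.5).

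Route (a) costs two short form items and protocol wording. Route (b) costs wording only, but leaves events before discharge unrecorded.

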### 10.2 Recording and Assessment of Serious Adverse Events

Safety outcomes (readmission, ED visits, GP encounters, death) form an integral part of the study design and will be collected retrospectively at all follow up stages (1, 3 and 6 months after the intervention).

A possible causal dependence of individual SAEs on the study intervention will be assessed by the study team according the following definitions:

|                   |                                                                                                                                                                                                                                                 |
|-------------------|-------------------------------------------------------------------------------------------------------------------------------------------------------------------------------------------------------------------------------------------------|
| Unrelated: | 

• The event started in no temporal relationship to the medical intervention applied and

• The event can be definitely explained by underlying diseases or other situations.

             |
| Related:   | 

• The event started in a plausible temporal relationship to the medical intervention applied and

• The event cannot be definitely explained by underlying diseases or other situations.

 |

### 10.3 Reporting of Serious Adverse Events

All SAEs will be summed up in the annual safety report (ASR) and submitted to the CEC. The ASR will contain a summary of the events including severity and causal relationship to the intervention and implications on the safety of participants. The enclosed letter to be provided with the ASR will contain a short summary of the status of the clinical trial.

### 10.4 Follow up of (Serious) Adverse Events

Any participant terminating the study (either regularly or prematurely) with a reported ongoing SAE will remain in the medical care of his attending physician who will provide clinical monitoring until a final evaluation after termination of the SAE.

Follow-up investigations may also be necessary according to the investigator's medical judgment even if the patient has no SAE at the end of the study.

Information related to clinical monitoring and follow-up investigations will be noted in the source documents.

## **10.5 Urgent Safety Measures**

Any finding or result of the trial that might jeopardize all participants' safety and requires immediate preventive or corrective action will be reported to the CEC within 48 hours.

## **10.6 Early Termination of the Study due to Safety Concerns**

The sponsor-investigator can terminate the study at any point of time in case of substantial ethical or participant safety concerns associated with continuing the study.

## 11 STATISTICAL METHODS

### 11.1 Hypothesis

- A simple medication review tool in combination with a defined communication strategy at hospital discharge leads to longer hospital readmission times compared to usual care at discharge (control group)
- and has the potential to improve the patients' health outcomes and quality of life (see secondary outcomes in section 5.2).

### 11.2 Determination of Sample Size

We modeled hospital readmission time by fitting an exponential survival curve on published readmission rates (48, 46) and internal data from the University Hospital Zurich. Extending readmission time by 25% was considered a relevant effect of the intervention. In the fitted model, this translates into an increase of the median readmission time by 23.2 days (from 92.7 days to 116.8 days) and corresponds to a hazard ratio of 0.80 between intervention and control group participants. This is equivalent to a decrease of 18.2% in readmission rates after 30 days (from 20.1% to 16.4%).

Based on this hazard ratio and assuming a two-sided  $\alpha = 5\%$ , a power of  $1 - \beta = 80\%$ , an intraclass correlation coefficient (ICC) of 0.02 as in (18), 40% overall censoring probability and equally sized clusters of 50 patients, we calculated a sample size of 21 clusters and 1'050 individuals per trial arm. Thus, 42 senior HPs and 2'100 patients in total will need to be included in order to observe a relevant effect of the study intervention with sufficient power.

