| Number of Participants with Rationale: | 
Based on published readmission rates, an exponential survival curve has been modeled. We defined a delay in time to readmission of 25% as relevant. This translates into a difference in medians of 23 days (from 93 to 116 days) and corresponds to a hazard ratio of 0.80 between intervention and control group participants. We assumed a two-sided alpha of 0.05, a power of 80%, an intraclass correlation coefficient (ICC) of 0.02, an overall censoring probability of 40%, and a cluster size of 50 patients per senior HP. Thus, 21 senior HPs and 1’050 patients per arm are needed, i.e. 42 senior HPs and 2’100 patients in total.
 
An interim analysis with 50% of the full sample size is planned in case of poor recruitment success.
                                                                                                                                            |
| Study Duration:                        | Patients will be recruited during 4 months or until the designated number of patients per cluster is reached, and follow up will last for 6 months for each patient.                                                                                                                                                                                                                                                                                                                                                                                                                                                                                                                                                                                                                                                                                                                                           |

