#### *b. The hospital discharge issue*

Readmission after hospital discharge is a frequent event: In the US, one in 5 hospitalized Medicare beneficiaries is readmitted within 30 days, at a cost of more than \$ 26 billion per year (19). In the recent years 2011 and 2012, these rates were quite stable, at 19% and 18.4%, respectively (12). In a German health assurance claims sample from 2003, the 30-day readmission rate among a sample of nearly 200'000 patients was very similar with 18.5% (47). Own (not published) data of the UniversityHospital of Zurich show a similar 30-day readmission rate of 17% and a 90-day readmission rate of 27% for multimorbid elderly patients ( $\geq 60$  years).

Studies using different discharge interventions show effects between 15% and 50% readmission rate reduction, mainly at the 30-day post-discharge time point (28, 48). A recent systematic review from the Cochrane Collaboration (13) demonstrated an average 13% relative risk reduction for readmissions by planned discharge interventions (RR 0.87; 95% CI 0.79-0.97) from 15 trials, and time to readmission could be extended by half (from 12 to 18 days) in a frail population of older adults ( $\geq 60$  years) by a transitional care program (46). Costantino et al. found that the earlier a multifaceted intervention took place after discharge from hospital the greater was the reduction in the readmission rate (7).

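### The sample-size model (constant hazard, 40% censoring) conflicts with the protocol's own 27% readmission at 90 days; if that rate applies to the trial outcome, 2,100 patients give clearly less than 80% power

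*Protocol*

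**What the plan says.** Section 11.2 of the protocol derives the sample size from a single exponential curve: "We modeled hospital readmission time by fitting an exponential survival curve on published readmission rates" and internal University Hospital Zurich data. The effect is a shift in median readmission time "from 92.7 days to 116.8 days", which "corresponds to a hazard ratio of 0.80 between intervention and control group participants". The 30-day readmission rates given for the two arms run "from 20.1% to 16.4" percent.

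The calculation then uses two-sided 5% significance, 80% power, an ICC of 0.02, clusters of 50 and "40% overall censoring probability". The result is 21 clusters and 1,050 patients per arm. The synopsis repeats these inputs: "We assumed a two-sided alpha of 0.05, a power of 80" percent, and "an overall censoring probability of 40" percent. Section 7.4 adds that the 40% also allows for dropouts. Follow-up for the primary outcome is 6 months (section 5.1).

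Section 3.3, part b, reports unpublished University Hospital Zurich data for multimorbid patients of 60 or older: a "30-day readmission rate of 17% and a 90-day readmission rate of 27" percent. The protocol gives no 6-month readmission rate.

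**The concern.** The power of a log-rank or Cox comparison depends on the number of events. The 40% censoring is the input that turns required events into required patients, and 60% with an event within 6 months is plausible only if readmissions continue at their early pace.

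The protocol's own figures for this population point the other way. From day 30 to day 90 readmissions come much more slowly than in the first month. The model's 90-day value is nearly double the only 90-day rate in the document, and that rate comes from the hospital named as a source of the fit. If it describes the trial population, the stated 80% is too high, and a null result could be read as coming from a better-powered trial than was run.

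**Working it through.** **1. The stated sample size is reproduced.** Required events for HR 0.80 with two-sided 5% and 80% power:
- Schoenfeld: 4 × (1.960 + 0.842)² / (ln 0.80)² = 631
- Freedman: (1.960 + 0.842)² × (1.80/0.20)² = 636

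Design effect: 1 + (50 − 1) × 0.02 = 1.98. Patients: 631 / 0.60 × 1.98 = 2,082, or 636 / 0.60 × 1.98 = 2,099. Both round up to 21 clusters per arm, that is 2,100 patients with 0.60 × 2,100 = 1,260 events. Power at 2,100 is 80.4% (Schoenfeld) or 80.0% (Freedman). The arithmetic is sound; the question is the 60% event fraction.

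**2. What the fitted curve implies.** Daily control hazard = ln 2 / 92.7; the intervention hazard is 0.80 times this.

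| Day | Control | Intervention |
|---|---|---|
| 30 | 20.1% | 16.4% |
| 90 | 49.0% | 41.6% |
| 180 | 74.0% | 65.9% |

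The day-30 row matches section 11.2, so this is the model used. The mean event fraction at day 180 is 69.95%, so administrative censoring alone is about 30%. Reaching 60% means keeping 0.60 / 0.6995 = 86% of events, an implied loss of about 14%.

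**3. What section 3.3 implies.** Cumulative hazard is −ln(0.83) = 0.1863 at day 30 and −ln(0.73) = 0.3147 at day 90. The daily hazard is 0.1863 / 30 = 0.0062 up to day 30 and (0.3147 − 0.1863) / 60 = 0.0021 from day 30 to day 90, about one third. Under a constant hazard, 17% at day 30 would give 1 − 0.83³ = 43% at day 90, not 27%. The Weibull shape through both points is ln(0.3147 / 0.1863) / ln 3 = 0.48.

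**4. Extrapolation to day 180.** The documents give no 6-month rate, so three curves are shown. The first two pass through both points. The third passes through the 27% only and is the most favourable to the plan.

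| Curve | Control | Intervention (HR 0.80) | Mean | Events of 2,100 |
|---|---|---|---|---|
| Weibull | 35.5% | 29.6% | 32.5% | 683 |
| Day 30-90 hazard continued | 39.8% | 33.4% | 36.6% | 768 |
| Single exponential through 27% | 46.7% | 39.6% | 43.1% | 906 |

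Censoring before dropout is 57-67%. Taking 6 months as 182.5 days moves the third curve to 915 events and 56% censoring, with little change elsewhere.

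**5. Power at HR 0.80 with the protocol's design effect.** Power = Φ(0.2231 × √(events / 1.98) / 2 − 1.96).

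| Curve | No dropout | With 14% loss |
|---|---|---|
| Weibull | 54% | 48% |
| Day 30-90 hazard continued | 59% | 53% |
| Single exponential through 27% | 67% | 60% |

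The HR detectable with 80% power, exp(−2 × 2.802 / √(events / 1.98)), is 0.74, 0.75 and 0.77 before dropout.

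**6. Sensitivity to the design effect.** If clustering inflation is tied to events per cluster, 1 + (50 × event fraction − 1) × 0.02, power is about 72-81% without dropout and 67-76% with the 14% loss. At the planned 60% event fraction this gives a design effect of 1.58 and 88% power, so it is not the method behind 2,100.

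**7. A side slip.** 116.8 − 92.7 = 24.1 days, not the stated 23.2; 92.7 × 1.25 = 115.9, which does give 23.2.

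**The case against.** Four points on the other side have weight.

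- **The fit has several sources.** Two published studies also entered it, and their rates are not in the document. A pooled curve need not pass through every input, and the modelled 20.1% at 30 days is close to the 17-20% cited in section 3.3. This stands as a limit on the conclusion. It does not remove the misfit at 90 days, which the protocol leaves unexplained.
- **The 27% may not measure the trial outcome.** Section 3.3 does not say whether returns to other hospitals were counted. The trial collects readmissions through patients, relatives, GPs and hospitals, across sites of all levels. If the internal figure covers same-hospital returns only, it understates the trial's event rate. This stands, and makes the power figures conditional.
- **Six-month rates are extrapolated.** A reader might infer that the design simply has 55-60% power. The documents do not support a single figure or so narrow a band: it needs two chosen curves, no dropout and the 27% as the true trial rate.
- **The design effect matters.** Under the events-per-cluster version the shortfall is smaller, and in the most favourable case it disappears. The figure of 1.98 is kept here because only it reproduces the plan's number.

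Two further inferences are tempting and should not be drawn. One is that the trial cannot observe its target because the median may not be reached within 6 months: the planned comparison is log-rank and Cox, and the medians only illustrate the HR. The other is that, under a Weibull of shape 0.48, 25% more time means HR 1.25^−0.48 = 0.90: section 11.2 makes the 25% translation within its exponential model and bases the sample size on HR 0.80.

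**Conclusion.** The internal contradiction is firm. The model puts half of controls back in hospital by about day 93, while the protocol's own data for this population show 27% by day 90, and its 30- and 90-day figures together rule out a constant hazard. The 40% censoring that fixes 2,100 patients is not supported by those figures.

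The size of the shortfall is conditional. It assumes that the 27% applies to any-hospital readmission, that the curve to 6 months lies within the range shown, and that the plan's design effect of 1.98 holds. On that basis every scenario falls short of 80%. The calculation from stated inputs to sample size is correct, and the slip in the medians does not affect it.

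**What to change.** In section 11.2 and the synopsis:

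1. Refit with a non-constant hazard (Weibull or piecewise exponential) that reproduces the 30- and 90-day figures of section 3.3, or explain why the 27% does not apply, for example because only returns to the same hospital were counted. Give the 6-month readmission proportion assumed in each arm.
2. Replace the 40% by the implied administrative censoring, with dropout as a separate allowance.
3. Restate power for 2,100 patients at HR 0.80 as a range over event rates, naming the design effect used; or state the HR detectable with 80% power (about 0.74-0.77 before dropout, with 1.98).
4. Change 116.8 to 115.9 days in section 11.2 so that it agrees with the 23.2-day difference.

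The cost is a rewrite of two passages and a less favourable power statement. No additional patients are required for the correction itself.
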